### Blood Tests

Patients will be asked to undergo a blood test at baseline and at the end of the intervention program to investigate the inflammation-, immune-, and oxidative aging–related measures. For chronic inflammation and immunity assessment, the BD Cytometric Bead Array system will be used to quantify the level of inflammation panel (interleukin-10, interleukin-12 p70, interleukin-1β, and interleukin-6), T helper 1 cells and T helper 2 cells panel (interleukin-2, interleukin-4, interleukin-5, tumor necrosis factor, and IFN-γ), B cell activation panel (CD79b, B cell linker protein, Btk, Syk, and PLCγ), T cell activation panel (TCRz, SLP-76, ZAP-70, Pyk2, Itk), and the complements panel (C4a, C3a, and C5a). The plasma level of C-reactive protein will be determined by the enzyme-linked immunosorbent assay. The oxidative aging maker in the plasma, including antioxidative enzyme activities of superoxide dismutase, glutathione peroxidase, and catalase as well as GSH (reduced form of glutathione), GSSG (oxidized form of glutathione), and malondialdehyde concentration, will be determined by colorimetric biochemical assays. For cardio-related markers, triglyceride, low-density lipoprotein cholesterol, high-density lipoprotein cholesterol, and total cholesterol will be tested. Fasting plasma glucose will also be evaluated. Blood vessel elasticity will be evaluated by the arterial velocity-pulse index and arterial pressure-volume index by a noninvasive PASESA detector (Win Horizon).

### Sample Size

The sample size for this study is based on the minimal important difference threshold of 2 points, which is the expected mean difference between groups [26]. Using a 2-sided hypothesis test at a significance level of .05 with an allocation ratio of 1:1, a sample size of 110 is calculated to achieve approximately 80% power to detect this effect size difference. Considering a 15% loss to follow-up or dropout rate, the final estimated sample size for this trial is 130.

### Feasibility and Process Evaluation

To assess the feasibility of the trial and the acceptability of the CP003 intervention, we will monitor the following process measures: (1) recruitment rate (ie, the number of participants enrolled per month), (2) retention and dropout rates at each study visit, (3) intervention adherence calculated based on the count of the remaining capsules and self-reported intake diaries, and (4) participant satisfaction with the intervention and study procedures assessed via a brief survey at the final visit. These measures will inform the practicality of conducting a larger definitive trial.

### Recruitment

Patients in this trial will be recruited through both advertisements and outpatient clinic enrollments in Hong Kong.

### Adverse Events

Adverse events will be assessed using the Treatment Emergent Symptom Scale and evaluated during the whole process as well as laboratory tests (eg, whole blood count, renal, and liver function tests), if needed. All clinical adverse events will be recorded in terms of intensity (mild, moderate, or severe), duration, outcome, and relationship to the study.

### Handling and Storage of Personal Data and Study Data

Data will be managed by and accessible only to authorized investigators and designated personnel on a password-protected system throughout the study period. In addition, an independent data and safety monitoring committee, separate from sponsors, researchers, and stakeholders, will convene quarterly to oversee the safety and effectiveness of the research in the medium term. The principal investigator will have access to the personal and study data during and after the study.

Our project team will ensure the security of raw data by storing it in a locked cabinet within a secure room with limited access. Data entry will be performed on a password-protected computer accessible solely to team members. Throughout and following the study, only designated team members will have the authority to access raw data or study records. Upon study completion, raw data will be preserved for a period of 5 years and subsequently disposed of, unless an application for extended retention is sanctioned by the institutional review board. Before statistical analysis, any personal identifying information will be expunged from the dataset.

### Data Processing and Analysis

The primary analysis will follow the intention-to-treat principle. The between-group difference in the primary outcome, defined as the mean change in the Chalder Fatigue Scale score from baseline to week 6, will be assessed using a generalized linear regression model, adjusted for the baseline score and stratification factors of CFS/ME versus post–COVID-19 fatigue. Results will be presented as the adjusted mean difference with a 95% CI. For participants lost to follow-up, inverse probability weighting will be used to address potential bias from missing data. Analysis of secondary outcomes and biomarker data will use similar generalized linear models at 6 and 12 weeks, adjusted for prespecified covariates, including time since COVID-19 infection, vaccination doses, routine exercise pattern, and baseline sleep quality. Subgroup analyses will be conducted based on gender, age category, and history of COVID-19 infection. Sensitivity analyses, including those using multiple imputation for missing data, will be performed. All analyses will be conducted using R software (version 4.5.2; R Foundation for Statistical Computing), with a 2-sided *P* value of <.05 considered statistically significant.

### Withdrawal and Dropout

If participants use a combination of treatments that are prohibited by the study protocol, withdraw their consent, or cease communication, they will be excluded from the study. Researchers will report the reasons for withdrawal and dropout and acquire the time of last treatment and outcome measures where possible.

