### Randomization and Blinding

After screening and baseline assessments, eligible participants will be randomly assigned to the CP003 intervention group or waitlist control group in a 1:1 ratio stratified by CFS/ME and post–COVID-19 condition. The CP003 intervention group received a therapeutic dose (5 capsules taken orally once per day for 6 weeks). The waitlist control group will wait for 6 weeks after the randomization and then start to receive CP003 capsules (5 capsules taken orally once per day for 6 weeks), followed by a 6-week follow-up. The random sequences generated in the R statistical package will have a block of 8 in each cycle, consisting of 2 CFS/ME control groups, 2 post–COVID-19 condition control groups, 2 CFS/ME intervention groups, and 2 post–COVID-19 condition intervention groups. Assignments were concealed in sealed opaque envelopes and were only opened after eligibility was confirmed and consent was obtained. The research study staff who recruit and screen the patients and the assessors who conduct baseline and follow-up assessments will be blinded to treatment allocation.

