### Interventions

Participants assigned to the intervention group will receive 5 CP003 capsules daily for 6 weeks, followed by a 6-week follow-up. CP003 is a Chinese medicine nutritional supplement used in Hong Kong, manufactured by Chinese Pharmaceuticals Co Ltd. Per the manufacturer’s guidelines, a complete treatment course consists of 6 weeks of CP003. Quality control will ensure that the similarity of multiple batches exceeds 96%, as tested by ultraperformance liquid chromatography with fingerprint analysis. During the intervention period, patients will be asked to complete a supplement intake diary to record any missed doses and any additional supplements taken. At the 6-week visit, participants are required to return any unused trial capsules.

The control group (ie, the waitlist) will wait for 6 weeks after randomization before receiving CP003 capsules and then start taking 5 capsules daily for 6 weeks, followed by a 6-week follow-up. During the waiting period, participants will be asked to complete a supplement intake diary to record any supplements they take in their daily lives. The overview of the study design is presented in Figure 2.

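### The rule that excludes participants for prohibited treatment is not reconciled with the intention-to-treat primary analysis

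*Protocol article*

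**What the plan says.** Withdrawal and Dropout attaches one consequence to three events. Where people take "treatments that are prohibited by the study protocol, withdraw their consent, or cease communication, they will be excluded from the study". The following sentence has researchers report the reasons and "acquire the time of last treatment and outcome measures where possible".

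Data Processing and Analysis states: "The primary analysis will follow the intention-to-treat principle". On missing outcomes it says: "For participants lost to follow-up, inverse probability weighting will be used to address potential bias from missing data". It adds: "Sensitivity analyses, including those using multiple imputation for missing data, will be performed".

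On the design, Randomization and Blinding says "The waitlist control group will wait for 6 weeks after the randomization". Blinding is stated for recruiting and screening staff, and "the assessors who conduct baseline and follow-up assessments will be blinded to treatment allocation". Participants are not listed as blinded.

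The primary outcome is the change in the Chalder Fatigue Scale from baseline to week 6, so the waiting period covers the whole primary endpoint window.

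**The concern.** Under intention-to-treat, participants are analysed as randomised whatever they do afterwards. Removing someone because they took a prohibited treatment is a per-protocol step. The article states both rules and does not say which governs when a participant has taken such a treatment and can still fill in the week-6 questionnaire.

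What is at stake is who enters the primary comparison. If the excluded participants differ in outcome from those retained, and the numbers excluded differ between arms, the two groups compared are no longer the two groups randomised. If who counts as excluded is settled only once data are visible, that choice can also be influenced by the results.

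**Working it through.** **The three events side by side**

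| Event named in the rule | Is the week-6 score obtainable? | What the analysis section provides |
|---|---|---|
| Prohibited treatment | Yes, the participant can still be assessed | Intention-to-treat implies use of the score; the rule says exclude |
| Consent withdrawn | Depends on what consent is withdrawn | Not addressed separately |
| Communication ceases | No, the outcome is missing | Weighting, with multiple imputation as sensitivity |

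Only the first row is a clear conflict. Exclusion can mean two things there:

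- Removal from the analysis: an observed week-6 score is discarded.
- End of participation before week 6: the outcome is sought only where possible, so the rule itself produces missing data.

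Neither reading delivers the stated primary analysis in full.

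**Reproducing the plan's figure**

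Inputs from Sample Size: difference 2 points, two-sided alpha 0.05, power about 80%, 110 evaluable (55 per arm), 15% dropout.

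- Inflation: 110 / (1 − 0.15) = 129.4, rounded up to 130. The stated figure reproduces.
- That section gives no SD. The value implied by the normal two-means formula is 2 / [(1.960 + 0.842) × √(2/55)] = 3.74.
- Standard error of the difference at 55 per arm: 3.74 × √(2/55) = 0.71.

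**Size of a possible shift (all rates assumed)**

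Let f be the fraction of an arm removed, and d the mean change of those removed minus that of those kept. The full-arm mean is the retained mean plus f × d. With the same d in both arms, removal shifts the between-group difference by (f control − f intervention) × d in absolute size.

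| Control removed | Intervention removed | d = 2 | d = 4 |
|---|---|---|---|
| 5% | 5% | 0 | 0 |
| 10% | 5% | 0.1 | 0.2 |
| 15% | 5% | 0.2 | 0.4 |
| 20% | 5% | 0.3 | 0.6 |

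The range is 0 to 0.6 points, or 0% to 30% of the 2-point target. The zero row depends on d being equal in both arms.

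Direction: if the removed controls were doing worse, the retained controls look better and the treatment effect is understated. If the other treatment had helped them, the effect is overstated.

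**Effect on error rate and power**

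- With no true effect and a standard error of 0.71, shifts of 0.2, 0.4 and 0.6 points raise the two-sided error rate from 5% to about 5.9%, 8.7% and 13.4%.
- With SD 3.74, power is 86.1% if all 130 are analysed and 80.0% with 110. It is 75.7% with 99, which is 110 less a further 10% removed by the rule. If the 15% allowance was meant to include such exclusions, the last figure does not apply.

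**The case against.** The strongest reply is that the rule sits under a heading about withdrawal and speaks of exclusion from the study, not from the analysis. The sentence on acquiring outcome measures would have little purpose if those participants were to be discarded. Read with the analysis section, it could mean that participation ends, outcomes are sought and everyone is analysed as randomised. This stands in part: a reader might infer that the plan certainly drops these participants from the primary analysis, and the text does not establish that. But nothing says the acquired outcomes enter the primary analysis, and ending participation early still loses scores that could have been collected.

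A second reply is that the Abstract describes weighting for missing data in general, which would cover scores lost through the rule. It would not cover a score that was observed. Weighting also repairs induced missingness only as far as its covariates explain it.

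A third is that a statistical analysis plan, not shown, may define the analysis set. For that reason the lack of a list of prohibited treatments is not counted here. The point concerns two stated rules that do not fit together.

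Three stronger readings are tempting, and the documents do not support them:

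- **Loss of contact contradicts intention-to-treat.** Those outcomes are missing under any rule, and the analysis section covers them.
- **The diaries conflict with the rule.** In Interventions, waitlist "participants will be asked to complete a supplement intake diary to record any supplements they take in their daily lives", but the intervention arm also records additional supplements. Recording use does not permit it, and a diary may be how prohibited use is detected.
- **Exclusion depends on arm.** This is plausible when participants know they are waiting untreated. However, no rates are given, and waitlist participants have a reason to comply because they receive CP003 after 6 weeks.

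**Conclusion.** The concern holds for prohibited treatment: the exclusion rule and the intention-to-treat primary analysis are not reconciled, and on either reading the rule discards or creates missing week-6 outcomes because of a post-randomisation event. It is an unresolved conflict between stated rules, not proof that participants will be dropped.

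The size cannot be computed from the documents. The range of 0 to about 0.6 points rests on assumed removal of 5% to 20% of controls and 5% of the intervention arm, with a deviation of 2 to 4 points. The upper end is demanding, since 4 points is twice the target difference and slightly above the implied SD of 3.74. The direction is unknown. The error rates further assume that SD and 55 analysed per arm.

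The conflict should be settled before analysis, because it decides who enters the primary comparison.

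**What to change.** Reword Withdrawal and Dropout so that it removes no one from the analysis set, and state the following there or in the analysis section:

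- All randomised participants are analysed in their assigned arm.
- Outcomes observed after prohibited treatment are kept and used in the primary analysis.
- Outcome collection continues where still possible unless consent to follow-up is withdrawn. Data already collected are kept as consent allows.
- Loss of contact is missing data, handled by the stated weighting with multiple imputation as sensitivity.
- Exclusion for co-treatment appears only in a supplementary per-protocol analysis.

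This concerns data collection and analysis only. It takes no position on which treatments are prohibited or on whether study capsules continue.

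The wording costs about one paragraph. The Results section reports that recruitment ended in September 2025 and that no data had been entered by December 2025, so the analysis set can still be fixed before results are seen. Continued week-6 collection may come too late for most participants. Where scores were not sought because of the rule, their number by arm should be reported. The downside is that the estimate includes any effect of co-treatment, which intention-to-treat already implies.

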### Consent or Assent

Research staff will ask interested participants to provide consent via the secure REDCap electronic consent platform. Participants will receive information regarding the trial electronically and have the opportunity to discuss the trial specifics and meet with a research team member, virtually or in person, before deciding on participation.

### Dissemination Policy

Upon study completion, the main findings will be disseminated to patients, primary care providers, and physicians through the hospital authority network in Hong Kong. Results will be presented at academic conferences and published in peer-reviewed journals.

## Results

This is a study protocol, and no results from the trial are available at this stage. This study received funding in March 2024 (grant ITF/PRP/029/24FX). Participant recruitment concluded in September 2025. Follow-up for each patient will be 6 weeks. The total duration of the study will be approximately 24 months. As of December 2025, all participants had been enrolled, but data entry had not yet commenced. Data collection, including baseline and all follow-up assessments, will proceed according to the timeline presented in Figure 2. Data analysis will commence after all participants complete the 12-week follow-up. Results are expected to be submitted for publication in mid-2026. Upon trial completion, we will report the between-group differences in primary and secondary outcomes, such as the Chalder Fatigue Scale, Fatigue Severity Score, SF-36, PROMIS fatigue 7a, HADS, and the Pittsburgh Sleep Quality Index, at the 6- and 12-week time points. Changes in inflammatory, immune, and oxidative stress biomarkers from baseline to the end of intervention will also be presented. Safety outcomes will be assessed through adverse event monitoring, and laboratory tests will be reported.

In case of any changes to the protocol, the investigators, clinical research assistants, the ethics committee, and the sponsor will be immediately informed via email.

## Discussion

Our protocol uses a randomized, waitlist-controlled trial design to achieve two primary objectives: (1) systematically evaluate the efficacy and safety of CP003 for CFS/ME and post–COVID-19 fatigue management and (2) elucidate clinical correlations between CP003 and key biomarkers of inflammation, immune function, and oxidative stress to reveal potential therapeutic mechanisms. This design was selected based on 3 key considerations. First, the waitlist-controlled approach balances scientific rigor with ethical considerations by ensuring that all participants eventually receive the intervention while avoiding placebo-related ethical concerns in this vulnerable population [27]. Second, our dual clinical-biomarker assessment strategy overcomes limitations of purely subjective measures by combining validated questionnaires (ie, the Chalder Fatigue Scale) with quantitative biomarker analysis (eg, interleukin-6 and superoxide dismutase), as recommended by the International Consensus Criteria [28]. Third, our sample size (N=130) was powered to detect clinically meaningful 20% fatigue score reductions (α=.05 and power=80%) while accounting for 15% attrition, ensuring both statistical robustness and practical feasibility [29].

However, this study is subject to several limitations. The heterogeneity inherent in fatigue-related disorders, particularly the symptomatic overlap with conditions such as depression and fibromyalgia, may influence treatment response and generalizability. Although standardized fatigue scales were used, the primary efficacy evaluation remains dependent on patient-reported outcomes in the absence of definitive biomarkers. In addition, the 12-week study duration, comprising a 6-week intervention and 6-week follow-up periods, may be inadequate to fully assess the long-term benefits or potential risks associated with prolonged lingzhi administration. Future studies with extended observation periods and more rigorously stratified participant cohorts are warranted to corroborate these initial findings.

In conclusion, this trial adds to the expanding evidence base for natural interventions in fatigue-related conditions and provides new insights into the therapeutic potential of lingzhi as a TCM-derived agent. Should efficacy be established, subsequent research ought to prioritize several directions: (1) refining dosage and treatment protocols through dedicated dose-finding studies, (2) conducting comprehensive long-term safety evaluations in extended longitudinal settings, and (3) elucidating the underlying mechanisms in broader and more diverse patient populations. This study emphasizes the value of integrating traditional medicine with contemporary research frameworks to tackle complex, multifactorial syndromes, such as CFS/ME and post–COVID-19 fatigue syndrome, while underscoring the promising yet underexplored role of TCM-based formulations, such as lingzhi.

## Appendix

Multimedia Appendix 1 Peer-review report from The Innovation and Technology Commission Grant (Hong Kong).

## Abbreviations

CFS: chronic fatigue syndrome
HADS: Hospital Anxiety and Depression Scale
ME: myalgic encephalomyelitis
PROMIS: Patient-Reported Outcomes Measurement Information System
REDCap: Research Electronic Data Capture
SF-36: 36-Item Short Form Health Survey
TCM: traditional Chinese medicine
